## Abstract

**Background:**

Social media (SM) use constitutes a large portion of midadolescents’ daily lives as a way of peer interaction. A significant percentage of adolescents experience intense or problematic social media use (PSMU), an etiologically complex behavior potentially associated with psychological distress. To date, studies longitudinally testing for risk or protective factors of PSMU, and collecting qualitative data are still scarce among midadolescents. Self-help interventions specifically targeting PSMU in this population and involving midadolescents in co-creation are needed.

**Objective:**

The 2-year SMART multicenter project aims to (1) advance knowledge on PSMU; (2) co-design an unguided self-help app for promoting awareness and functional SM use; and (3) test feasibility and provide preliminary findings on its effectiveness to further improve and adapt the app.

**Methods:**

The SMART project is organized in 3 phases: phase 1 will focus on knowledge advancement on PSMU and its risk and protective factors using a longitudinal design; phase 2 will explore adolescents perspectives using qualitative approach and will co-design an unguided self-help app for reducing PSMU, which will be evaluated and adapted in phase 3. Around 1500 midadolescents (aged 14-18 years) will be recruited in northern, central, and southern Italy to investigate the potential intra- and interpersonal psychological risk and protective factors for PSMU and define specific PSMU profiles and test for its association with psychological distress. Subjective (self-report) PSMU’s psychosocial risk or protective factors will be assessed at 3 different time points and Ecological Momentary Assessment (EMA) will be used. Moreover, focus groups will be performed in a subsample of midadolescents to collect the adolescents’ unique point of view on PSMU and experiences with SM. Those previous results will inform the self-help app, which will be co-designed through working groups with adolescents. Subsequently, the SMART app will be deployed and adapted, after testing its feasibility and potential effectiveness in a pilot study.

**Results:**

The project is funded by the Italian Ministry of University and Research as part of a national grant (PRIN, “Progetti di Rilevante Interesse Nazionale”). The research team received an official notice of research funding approval in July 2023 (Project Code 2022LC4FT7). The project was preregistered on Open Science Framework, while the ethics approval was obtained in November 2023. We started the enrollments in December 2023, with the final follow-up data to be collected within May 2025.

**Conclusions:**

The innovative aspects of the SMART project will deepen the conceptualization of PSMU and of its biopsychosocial antecedents among midadolescents, with relevant scientific, technological, and socioeconomic impacts. The advancement of knowledge and the developed self-help app for PSMU will timely respond to midadolescents’ increased loneliness and psychological burden due to COVID-19 pandemic and humanitarian crisis.

**Trial Registration:**

OSF Registries; https://osf.io/2ucnk/

**International Registered Report Identifier (IRRID):**

DERR1-10.2196/58739

## Introduction

### Background

According to the World Health Organization, one-sixth of the global population is composed of adolescents, and this number is expected to rise through 2050 [1]. Unfortunately, 1 in 7 adolescents experience mental health conditions, which remain largely unrecognized and untreated. Also, given the widespread use and pervasiveness of new technologies among adolescents, it is not surprising that 60.43% of Italian adolescents report an intense or a problematic social media (SM) use (PSMU) [2] and, although to our knowledge, no estimations regarding the direct or indirect financial cost or societal burden of PSMU are currently available, it has been hypothesized that PSMU may have relevant costs both for individuals (eg, mental and physical health, social functioning) and societies (eg, direct health care costs and indirect costs following productivity losses).

SM is made up of various digital user-driven platforms (eg, Facebook, TikTok, Instagram) that facilitate connectivity and engagement between individuals as well as allow to create and share user-generated content [3]. PSMU is considered an etiologically complex behavior associated with psychological distress, although this relation is far from being completely understood [4] and the conceptualization of PSMU is still debated. To date, the absence of a commonly accepted definition could be linked to the rapidly changing nature of SM as well as to the inconsistent results obtained by prior research on PSMU among adolescents [5]. Technology and SM are an integral part of the daily life of today’s teenagers, who use them to create a virtual space to satisfy their needs for communication, social contact, belonging, comparison, and self-realization. However, some scholars defined PSMU as an “addictive-like” behavior (eg, associated with salience, tolerance, withdrawal, and relapse) [6], hierarchically arranged (ie, with different levels of excessive or disordered use) and whose main characteristic is a lack of self-regulation in one’s own SM use [4].

Nonetheless, the adoption of an addiction paradigm to describe PSMU has been criticized [7].

Further, recent findings have highlighted how PSMU cannot be defined solely by the so-called screen-time (“how much”), but rather by “how” the SM is used [8]. More specifically, a high intensity of screen time and SM use may be a normative adolescent behavior that does not necessarily interfere with life domains relevant to adolescents’ mental health (eg, offline socializing with friends or family) [2]. Core aspects of the way in which SM are used are active versus passive use [9], social support [10], fear of missing out [11], and types of activities individuals engaged in when using SM [12]. Yang et al [13] proposed an integrative model in which the previous multiple dimensions of SM use are considered. The Multidimensional Model of Social Media Use [13] suggests that individual platforms differ by activities (eg, interactive or directed communication, active posting to an unspecified audience, passive browsing), motives for use (eg, enhancement or compensation), and communication partners (eg, strong or weak ties) and that each dimension is associated with better or poorer well-being among youth. However, despite these differences in SM platform activities and interaction partners, surprisingly research usually focuses on overall or generic SM use and few studies have examined how adolescent characteristics may be more relevant to some platforms than others [14,15].

Previous research has also investigated several potential intra- and interpersonal psychological predictors of PSMU, clearly evidencing its multifactorial and complex etiology [16]. Among others, secure attachment [17], self-esteem [18], self-control [19], emotion regulation [20], life satisfaction [21], and parental variables (such as low levels of parents’ own SM use and parental phubbing) [22] are some of the established protective factors for PSMU. Despite such efforts, the mechanisms underlying the development and maintenance of PSMU are still underinvestigated [4,23] due to the lack of (1) well-performed longitudinal studies designed to test for a temporal precedence of specific risk and protective factors for PSMU, (2) qualitative studies collecting adolescents’ unique perspectives and needs, and (3) psychophysiological studies on PSMU. Indeed, 2 biomarkers of psychopathological risk, namely a lower parasympathetic activity over heart at rest [24], and the presence of specific polymorphisms for serotonin gene transporter 5-HT1AR and 5-HT2AR [25], may be associated with increased odds of PSMU among adolescents.

Finally, there is a call for effective prevention or early intervention programs which are tailored to the substantial risk and protective factors for PSMU to promote awareness of PSMU phenomenon and functional SM use and to overcome less effective abstinence-based protocols [26]. Smartphone apps could be an innovative way to reach young people. There is increasing evidence that unguided mobile self-help apps and web-based interventions offer a powerful solution for promoting public health and life skills interventions [27,28], especially among young digital natives [29,30]. The use and the engagement of such self-help apps may also increase thanks to a co-design process that involves end users (ie, midadolescents) [27,30,31].

### Objectives of the SMART Project

The 2-year project “problematic Social Media use among Italian mid-Adolescents: from the identification of Risk/proTective factors to the co-design and evaluation of a self-help app” (namely “SMART project”) aims to: (1) advance knowledge on PSMU and its risk and protective factors using a longitudinal design; (2) exploring adolescents unique perspectives on PSMU and co-design an unguided self-help app for promoting awareness and functional SM use; and (3) test feasibility and provide preliminary findings on its effectiveness to further improve and adapt the app.

As for the first aim, we hypothesize that intrapersonal (ie, higher difficulties in emotion regulation, negative affect, adjustment difficulties, and fear of missing out, as well as lower self-esteem, self-control, and satisfaction with life) and interpersonal (ie, attachment insecurity, higher preference for online social interactions, and parental phubbing and parents’ dysfunctional SM use) risk factors will predict higher adolescents’ PSMU (primary outcome), as well as higher emotional distress and passive SM use (secondary outcomes).

As for the second aim, the research questions that guide the study are: what are the adolescents’ experiences and perspectives on SM and PSMU, the SM impact, and the possible strategies for promoting positive SM use? As for the app, we hypothesize to include several interactive modules, including an informative and awareness section and a psychoeducational section, to promote both (1) emotional awareness and skills, and (2) adolescents’ personal and interpersonal resources, so to prevent PSMU and promote a functional SM use.

As for the last aim, we hypothesize a good feasibility for the SMART app, and that greater app use will be associated with an increase in functional SM use.

## Methods

### Study Design

The SMART project is organized in 3 consequential phases, each including different integrated actions: phase 1—prospective longitudinal study with repeated-measures design [32] for the advancement of knowledge on PSMU through quantitative approaches; phase 2—qualitative focus group study for exploring adolescents’ perspectives on PSMU and functional use of SM and co-design approach for developing the unguided self-help SMART app; phase 3—pilot study to evaluate feasibility and signal of effectiveness of the intervention throughout the self-help app.

The project is conducted by researchers and clinical psychologists in four Italian Universities (University of Verona, University of Palermo, University of Perugia, and University of Bergamo), thus including a large population of midadolescents in diverse regions of north, central, and south of Italy (see Figure 1 for an overview of the project phases and Table 1 for a synthetic description of general objectives, research aims, and methods of each phase).

**Figure 1 figure1:**
[figure not shown]
SMART project: General overview of the 3 phases.

**Table 1 table1:** General description of the 4 study phases: objectives, research aims, and main methodologies.

Phase	General objectives	Research aims	Main methodologies
Phase 1: Longitudinal prospective study	Improving the conceptualization of PSMU^a^ Longitudinally identifying the intra- and interpersonal risk, protective and maintenance factors of PSMU Longitudinally analyzing the associations between PSMU and psychological distress Exploring the presence of specific profiles of PSMU among adolescents Informing the development of SMART self-help app	Which are the main risk or protective factors of PSMU among adolescents? What are the longitudinal associations between PSMU and psychological distress? Is PSMU predicted by a higher distress, or is it a change in distress for that specific participant to predict it? Are there specific sub-groups of PSMU? If yes, what characterizes them?	Prospective longitudinal study with repeated-measures design (3 waves) using self-report questionnaires Collection of biological markers EMA^b^
Phase 2: Qualitative study and co-design of the SMART app	Exploring adolescents’ experiences, examples and perspectives on PSMU and functional use of SM^c^ Informing the development of SMART self-help app Co-designing the beta version of a self-help app aiming to promote awareness and functional SM use	Which are the adolescents’ experiences and perspectives on PSMU and functional use of SM? Which are the adolescents' opinions and perspectives on what is useful to promote awareness and functional SM use? Which are the adolescents’ perspectives, suggestions, and preferences on an app to promote functional SM use?	Focus groups Thematic analysis of the transcripts to identify and analyze patterns in qualitative data Co-design working groups with the adolescents involved
Phase 3: Feasibility and pilot study	Investigating the feasibility and acceptability of the SMART self-help app Preliminary evaluating its effectiveness Incorporating user feedback and study results during the app development	Which are the perspectives of adolescents on the SMART self-help app feasibility and acceptability? Is there preliminary evidence that the SMART self-help app is effective?	Single-arm pilot feasibility study to explore feasibility and preliminary data on effectiveness (pre-post evaluation)

^a^PSMU: problematic social media use.

^b^EMA: ecological momentary assessment.

^c^SM: social media.

### Participant Recruitment and Setting

The target group (adolescents aged 14-18 years) will be actively involved in the various actions of each phase. Participants will be recruited from schools (ie, secondary school), in the north, central, and south Italy. Each research team will select schools (on a voluntary basis or following previous collaborations) and interact with stakeholders (regional and local school offices, school communities) to obtain their availability for participation. Attention will be given to contacting schools located in particularly disadvantaged areas and to include students with different sociodemographic and cultural backgrounds and levels of vulnerability. At each participating school, adolescents may participate in the different phases of the study.

The following inclusion criteria will be followed for participation in each included school: (1) having an age between 14 and 18 years, (2) having signed the consent form for the study participation (ie, consent to participate for adolescents less than 18 years signed by both parents—or legal representatives—or by the adolescent when 18 years); having sufficient knowledge of the Italian language.

### Procedure and Measures

#### Longitudinal 3-Waves Evaluation (Phase 1)

The longitudinal evaluation study (phase 1) will be articulated across 3-time points of assessment: baseline (T0: around months 3-5), at around 5 months (T1: months 8-10), and at around 10 months follow-up (T2: month 13-15). At each time point, a survey composed by a battery of self-reported questionnaires will be delivered through a dedicated web-based platform during regular school hours.

Diverse theoretical models of PSMU are operationalized in those battery of questionnaires (see Table 2 and Multimedia Appendix 1 for a detailed description of measures and questionnaires) to explore potential intra- and interpersonal psychosocial risk or protective factors of PSMU.

**Table 2 table2:** Self-report questionnaires adopted in the SMART project^a^.

Role of the dimension in the longitudinal study ad questionnaire name			Investigated dimension		Questionnaire’s characteristics		Time
**Intrapersonal risk factors**							
	Difficulties in Emotion Regulation Scale-Short Form [33]	Emotion dysregulation		18 Items, 5-points Likert scale		T0, T1, and T2	
	Rosenberg Self-Esteem Scale [34]	Self-esteem		10 Items, 5-points Likert scale		T0, T1, and T2	
	Brief Self-Control Scale [35]	Self-control		13 Items, 5-points Likert scale		T0, T1, and T2	
	Satisfaction With Life Scale [36]	Satisfaction with life		5 Items, 7-points Likert scale		T0, T1, and T2	
	Strengths and Difficulties Questionnaire [37]	Adjustment difficulties and strengths		25 Items, 3-points Likert scale		T0, T1, and T2	
	Fear of Missing Out Scale [38]	Apprehension that others might be having rewarding experiences from which one is absent		10 Items, 5-points Likert scale		T0, T1, and T2	
**Interpersonal risk factors**							
	Inventory of Parent and Peer Attachment—Revised [39]	Attachment relationships toward mother, father, and peers		25 Items, 5-points Likert scale		T0	
	Preference for Online Social Interaction Scale (subscale of the Generalized Problematic Internet Use Scale 2) [40]	Preference for online social interaction		3 Items, 5-points Likert scale		T0, T1, and T2	
	Parental Phubbing Scale [41]	Perceived parental phubbing		9 Items, 5-points Likert scale		T0, T1, and T2	
**Primary outcome**							
	Bergen Social Media Addiction Scale [42]	Core addiction elements regarding SM^b^ use		6 Items, 5-points Likert scale		T0, T1, T2, and T3	
**Secondary outcomes**							
	Social Emotional Distress Scale—Secondary [43]	Emotional distress		10 Items, 4-point Likert scale		T0, T1, T2, and T3	
	Passive Social Networking Site Use Questionnaire [44]	Passive SM use		5 Items, 5-points Likert scale		T0, T1, T2, and T3	

^a^Time: time of administration; T0 (baseline) corresponds to months 3-5, T1 to months 8-10, and T2 to months 13-15. T3 is an additional time point (at the end of the app intervention) explained in phase 3.

^b^SM: social media.

Moreover, in a subsample of participants, momentary emotions or feelings (eg, happy, sad, tired, relaxed, nervous, quiet, each rated on a visual analogue scale) as well as the subjective use of SM during the past 2 hours will be recorded at 1 time point through an ad hoc app, using an ecological momentary assessment approach [45]. Momentary questions will be randomly delivered during nonschool hours (ie, from 3 to 10 PM), for a total of 4 times per day, for 2 weeks.

At baseline, 2 additional biological markers of PSMU will be randomly collected in vivo in a subsample of participants. First, the autonomic activity of the participants will be collected with the aim of testing whether a greater PMSU is associated with a decreased vagal (ie, parasympathetic) activity at rest. This autonomic parasympathetic activity—considered a physiological index of emotion dysregulation [24]—will be investigated through specific indices of heart rate variability (HRV) such as the high frequencies and the root mean square of successive differences between normal heartbeats [46]. The HRV will be continuously recorded during 10-minute resting condition using a wearable electrocardiogram device. The second biomarker is the presence of specific polymorphisms for serotonin gene transporter 5-HT1AR and 5-HT2AR that—according to the bipartite model of brain serotonin functions [25]—seem to be associated with a greater risk of developing internalizing disorders [47], such as PSMU. The presence of these polymorphisms will be tested through saliva samples, collected with a saliva stick and processed by the University of Perugia.

#### Qualitative Focus Group Study and Co-Design Approach (Phase 2)

Focus groups (FGs) have been widely used as a method for exploring people’s perspectives and experiences by using the group interaction to encourage the participants to explain, disagree, and share their views [48]. This method is particularly useful in research with adolescents [49]. Through FGs, we will explore the adolescents’ point of view regarding the following topics: the adolescents’ perspectives regarding the main purposes and modalities of SM use; the link between SM use, psychological distress, and well-being; risk factors associated with PSMU and protective strategies and resources that may be activated to promote functional use of SM. Each FG will be led by a moderator and an assistant (both with expertise in conducting FGs and in clinical psychology) and will last around 90-120 minutes each. Each FG will include around 8 to 10 adolescents, recruited through purposive sampling in the participating schools and balanced for sociodemographic variables, according to the suggestions of Palinkas et al [50], and the availability of the participating schools.

FGs will be conducted following a shared interview guide, including a set of open-ended questions and following a semistructured approach. While conducting the FGs, researchers will also pay attention to the group dynamics, ensuring that a good atmosphere is maintained. Before the FG, participants will fill out a brief questionnaire to collect background information (eg, sociodemographic information, emotional distress, and SM use) to describe the sample.

Co-designing of the app involves “a process of collective creativity” based on active collaboration between researchers, developers, and end users (ie, midadolescents) as “experts of their experiences” [31,51]. Originating from the field of participatory design, the co-design process allows to maximize engagement, satisfaction, and use of eHealth interventions for potential users [29]. General guidelines for the application of co-design methods and previous research experiences of the research team will be followed to organize and structure the co-design workshops [27,51,52], adopting agile design, design thinking, and user-centered design approaches (ie, cycles of design, develop, and test) [29]. The timeframe and duration of the workshops will be agreed with participating schools. Specifically, a “designing group” (ie, 2 researchers in clinical psychology, 1 computer engineer, and a subsample of midadolescents) will be established at the beginning of the second phase of the project. Members will be involved in a series of interactive workshops (organized in presence or through digital platform meetings) to define the main functionalities, features and contents of the app (alpha version) on the basis of: preexisting conceptual models on PSMU, existing evidence-based interventions for, preliminary evidence from the sample of Italian midadolescents, including their experiences, suggestions, and needs. During the workshops, the facilitators will encourage midadolescents to discuss the topic presented through practical techniques (eg, use of visual materials, scenario thinking, playful activities, participants’ interactions with prototypes and discussion on them) [53] for facilitating co-design while promoting meaningful engagement among adolescents [29]. Ideally, in the first workshop, midadolescents will be asked to discuss the general aims, functionalities, features, and contents of the self-help app, while the subsequent workshops will aim to collect inputs for adapting the alpha version to a beta version.

#### Feasibility and Pilot Study (Phase 3)

In phase 3, the co-designed self-help app will be delivered to all recruited midadolescents, who will be free to download the app on their personal iOS or Android device. For 1 month, participants will be invited to use the self-help app exploring the different contents and functionalities weekly, and to adopt these newly learned competencies in their daily life.

At the end of the self-help app use (T3; postintervention), feasibility will be investigated: (1) administering an adolescent-adapted version of the “Mobile App Rating Scale user version” (uMARS) [54], together with open-ended questions exploring the adolescents’ opinion about the app (eg, “Can you tell me about your experiences using the App?”; “What did you like most/least?”). The uMARS is a 20-item self-report measure of the perceived quality of apps, which includes 4 objective quality subscales (ie, engagement, functionality, aesthetics, and information quality) and 1 subjective quality subscale.

At this last time point (T3; around months 18-20), we will gather preliminary data on the effectiveness of the app intervention, administering the self-report questionnaires measuring the primary and secondary outcomes mentioned in phase 1. Given that the latter time point for the longitudinal study (ie, T2) falls a little before the start of phase 3, data on outcomes collected at that time point will be used as preintervention scores.

As a last step of this project, the app (eg, contents, features, and design) will be adapted on the basis of the emerging results.

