In line with a mixed methods approach [71], quantitative and qualitative results will be synthesized and merged in order to achieve a better understating of the PSMU. Indeed, qualitative results will be used to deepen our understanding of the PSMU phenomenon, corroborating the findings from the quantitative design and/or adding potential different topics.

As for phase 3, feasibility (ie, uMARS mean scores and app usage) will be investigated through simple descriptives, examining whether participants met the thresholds for good feasibility: (1) mean uMARS subscale scores≥70% of the total will be considered indicative of good feasibility [72]; examining the app use (with ≥75% of participants with ≥10 app sessions considered indicative of a good feasibility) [72]. We will have a deeper understanding of the app feasibility by synthesizing the qualitative results. We will further examine whether the self-help app led to an actual change in primary and secondary outcomes through 3-level piecewise regression models, using the 4-time points from baseline (as defined in phase 1; T0) up to posttreatment (T3; M18-M20). To further strengthen these analyses, we will compute both a Reliable Change Index and a Clinically Significant Change for each participant [73,74]. These methods are used to test whether a change over time (in our case, from pre- to posttreatment) may be considered reliable (ie, taking into account the measure’s internal reliability) and clinically significant (eg, the posttreatment scores are within the boundaries of nonpathological scores).

Quantitative analyses will be performed using SPSS (version 29; IBM Corp), Hierarchical Linear Models (version 8.2; Scientific Software International, Inc), and MPLUS (version 8.4; Muthén & Muthén).

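### T2, the preintervention score, precedes the app by about 4 months on the article's own schedule, so about 80% of the T2-T3 interval is app-free

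*Protocol article*

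**What the plan says.** All statements are in the protocol article.

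- **T2.** The section on the three-wave evaluation places it "at around 10 months follow-up (T2: month 13-15"). The footnote to Table 2 agrees: "T0 (baseline) corresponds to months 3-5, T1 to months 8-10, and T2 to months 13-15".
- **App exposure.** The phase 3 section says: "For 1 month, participants will be invited to use the self-help app".
- **T3.** The same section puts it after exposure, "At the end of the self-help app use (T3; postintervention), feasibility will be investigated", and dates it: "At this last time point (T3; around months 18-20"). Statistical Analyses repeats the window: "up to posttreatment (T3; M18-M20").
- **Baseline for the pilot.** The phase 3 section reasons that T2 "falls a little before the start of phase 3, data on outcomes collected at that time point will be used as preintervention scores". Table 2 lists the primary and the two secondary outcomes at T0, T1, T2 and T3 only. No outcome assessment at app release is described.
- **Analysis.** Statistical Analyses asks whether the app changed the outcomes, by three-level piecewise regression "using the 4-time points from baseline (as defined in phase 1; T0) up to posttreatment (T3; M18-M20"). It adds a Reliable Change Index and a Clinically Significant Change for each participant, from pre to post.
- **Design and limitations.** Table 1 describes phase 3 as single-arm with a pre-post evaluation. The limitations paragraph names the nonrandomized design but not the time between T2 and the app.

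**The concern.** T2 is chosen as the baseline because it is said to lie close to the start of phase 3. If it does not, the pre-post interval consists mainly of months in which nobody has the app. Season, the school year, ageing or the project's own activities may change the outcomes in those months, and there is no control group to show by how much. The measured change could then create an apparent app effect or hide a real one.

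The pilot is meant to give preliminary findings on effectiveness, and the Discussion says that it may guide later randomized trials. A baseline that is further from the intervention than the text says weakens that use. This weakness is separate from the lack of randomization, and it can be avoided.

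**Working it through.** **Inputs.** T0 at months 3-5, T1 at 8-10, T2 at 13-15 (Table 2 footnote); T3 at 18-20, at the end of 1 month of app use (phase 3 section).

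**Reproducing the stated spacing.** T1 - T0 = 8 - 3 = 10 - 5 = 5 months. T2 - T0 = 13 - 3 = 15 - 5 = 10 months. Both match the article, so the windows can be read like for like.

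**App start.** The article gives no start month for the app. T3 minus 1 month fixes it: 18 - 1 = 17 to 20 - 1 = 19, that is, months 17-19.

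**Gap and app-free share.** Gap = (T3 - T2) - 1. Share = gap / (T3 - T2).

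| Case | T2 | T3 | T2-T3 (months) | Gap (months) | App-free share |
|---|---|---|---|---|---|
| Same place in both windows | 13, 14 or 15 | 18, 19 or 20 | 5 | 4 | 4/5 = 80% |
| Shortest | 15 | 18 | 3 | 2 | 2/3 = 67% |
| Longest | 13 | 20 | 7 | 6 | 6/7 = 86% |

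**Calendar check.** Assume that month 3 is December 2023, when enrolment began. T0 is then December 2023 to February 2024, T1 May to July 2024, T2 October to December 2024 and T3 March to May 2025. This fits the Results section, which reports T0 and T1 complete as of July 2024 and final data within May 2025. On this reading T2 falls in autumn and early winter, and T3 in spring.

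**What each analysis does with the gap.**

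- *Change indices.* They use the T2-T3 difference with no reference trend. A steady background drift of d per month contributes 5d, of which 4d arises before the app is available.
- *Piecewise model.* Three pre-app points allow a T0-T2 slope to be estimated, and a drift that continues unchanged can be removed. If the drift after T2 departs from that slope by d per month, the app-free months add about 4d to the contrast. With no measurement between T2 and T3, the model cannot tell those 4 months from the app month. Moving the knot to app start without new data would only extrapolate the T0-T2 slope across the gap.

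**Illustration.** The documents give no value for d. If it were 0.02 to 0.05 SD per month (an assumption), the app-free months would carry 4 × 0.02 = 0.08 to 4 × 0.05 = 0.20 SD. The whole interval would carry 5 × 0.02 = 0.10 to 5 × 0.05 = 0.25 SD. With a baseline at app release, 1 month of drift would remain: 0.02 to 0.05 SD.

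**The case against.** The case for the plan has real force on several points.

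- **Share of change.** A reader might infer that most of the change credited to the app happens without it. The documents do not show that. They fix the share of the interval, not of the change. Any app effect would fall in the last month, and its size relative to background change is unknown.
- **Knot.** A reader might take it that the model breaks at T2. Statistical Analyses does not say where the knot lies. T2 is a natural inference from its role as pre-score, but knot and time coding are details that an article may leave to the analysis plan.
- **Maturation.** A reader might say that all maturation is counted as app effect. For the piecewise model this is too strong, because a continuing trend can be removed. It applies without that qualification only to the two change indices, which are there to supplement the model.
- **Only signal.** The pre-post contrast is not the only evidence on effectiveness. The Objectives also hypothesize that greater app use goes with more functional use of social media, and app use is recorded.
- **Pilot status.** The feasibility thresholds concern app ratings and sessions, which T2 does not touch. The article already concedes that causal inference is limited. A fresh baseline would still leave an uncontrolled comparison.
- **Equal spacing.** The four waves are about 5 months apart, so T2-T3 can be set against two earlier intervals of the same length. A 1-month pre-post interval loses that.

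These points limit the claim and lower its weight. They do not remove the mismatch between the stated reason for using T2 and the stated windows. Nor do they let any planned analysis separate the app-free months from the app month.

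**Conclusion.** The point holds and should be fixed, though it does not undermine the pilot as a feasibility study. On the article's own windows, T2 precedes app start by about 4 months (2 to 6), and about 80% (67% to 86%) of the T2-T3 interval is app-free. The description of T2 as falling just ahead of phase 3 is not consistent with this.

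The change indices carry the whole interval. The piecewise model is protected against a trend that continues from T0-T2 but not against a change of trend after T2. The size and direction of any bias cannot be derived from the documents.

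The conclusion rests on two readings: that T3 closes the 1-month app period, as the text says, and that participants hold roughly the same place in the T2 and T3 windows. The range covers departures from the second.

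**What to change.** **Preferred.** Repeat the Bergen scale, the distress scale and the passive-use scale at app release: 6 + 10 + 5 = 21 items. Do this preferably on the same web platform and in the same school setting as T0-T2. Use these scores as the pre-scores for the change indices, and place the piecewise knot at app start. Keep T2 as a pre-app point, so that change over the app-free months is measured and the evenly spaced waves remain available.

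**Cost.** One more short session, a few minutes per participant (assumed), and a few sentences of text. The scales could instead be presented in the app at first login, but that has three drawbacks:

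- it changes mode and setting exactly at the break;
- it yields data only from those who download the app;
- it adds friction before first use in an app judged on at least 75% of participants reaching at least 10 sessions.

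**If a new assessment is no longer possible.** Replace the wording on the closeness of T2 with the actual interval of about 4 months. Code time in the model from actual assessment and app-start dates. State as a limitation that T2-T3 change, including reliable and clinically significant change, cannot be attributed to the app month. This costs only text and the recording of dates.
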